### 2.2. Trial Design

This will be a safety study of FMT for the prevention of NEC, in the form of a prospective, open-label study with continuous recruitment of up to 40 patients in total (20 in the study group, 20 in the control group). Included patients must meet the exact inclusion criteria described below and must not meet any exclusion criteria. The study group will include 10 premature infants born between 28 0/7 and 36 6/7 weeks of gestation, followed by another 10 premature infants born between 24 0/7 and 27 6/7 weeks of gestation, and 20 premature infants in the control group. After completion of this stage (inclusion and treatment of 20 patients + 20 in the control group), the safety of the therapy will be assessed with a description and presentation of all adverse events, their classification and relationship to the intervention.

The safety of the therapy will be assessed by comparison with a control group, i.e., 20 patients who will meet the same inclusion criteria and will not meet any of the exclusion criteria, subject to the same hospital observation but without undergoing any medical/therapeutic intervention other than the collection of biological material (including stool, blood and urine samples for exploratory testing of the gut microbiota).

Recruitment will occur continuously between January 2026 and January 2027. The study is registered at ClinicalTrials.gov (NCT06333405).

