#### 2.3.1. Sample Size

A formal sample size calculation based on power analysis was not performed, as this is a pilot safety study intended to generate preliminary data (estimates of adverse event rates) for a future randomized controlled trial (RCT). A sample size of 20 subjects in the intervention group was determined based on feasibility constraints and standard recommendations for pilot safety studies, following biostatistical consultation [28]. In the first phase, 10 patients born between 28 0/7 and 36 6/7 will be included, followed by 10 patients born between 24 0/7 and 27 6/7 in the second phase.

The control group will include 20 matched controls—patients who meet the same inclusion and exclusion criteria as the study patients.

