#### 2.3.3. Statistical Analysis

All analyses will be conducted on an intention-to-treat basis.

The primary endpoint is safety, defined as the incidence of adverse events (AEs) and serious adverse events (SAEs) during the observation period.

The proportion of patients experiencing at least one AE or SAE will be compared between groups using Fisher’s exact test. The chi-square test will be applied when its assumptions are met.

The incidence of specific AEs will also be compared using Fisher’s exact test. Relative risks (RRs) with two-sided 95% confidence intervals (CIs) will be calculated.

If the number of events per patient is analyzed, between-group comparisons will be performed using Poisson regression or negative binomial regression, depending on data dispersion.

Time to first AE, if applicable, will be analyzed using Kaplan–Meier estimates and compared using the log-rank test.

Continuous variables will be assessed for normality using the ShapiroWilk test. Normally distributed variables will be compared using Student’s *t*-test, and non-normally distributed variables using the Mann–Whitney U test.

Two-sided tests will be used throughout, with statistical significance set at α = 0.05. Estimates will be presented with two-sided 95% confidence intervals. Analyses will be performed using validated statistical software (e.g., R, Stata, or SAS); the exact software and version will be documented in the final report.

Given the limited sample size, the study is not powered for formal hypothesis testing of small effect sizes. Therefore, interpretation will focus primarily on effect size estimates and their 95% confidence intervals rather than solely on statistical significance. Clinically meaningful differences will be considered in the context of effect magnitude and precision.

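### For individual rare serious events, the relative risk, the only effect measure that Section 2.3.3 names for binary AEs, often has no usable value with 20 infants per arm

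*Protocol article*

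**What the plan says.** Section 2.3.3 compares the proportion of infants with at least one AE or SAE by Fisher's exact test, or by chi-square where its assumptions hold. For single event types it adds: "The incidence of specific AEs will also be compared using Fisher’s exact test". The effect measure follows: "Relative risks (RRs) with two-sided 95% confidence intervals (CIs) will be calculated". The section names no risk difference or odds ratio, and it states neither an interval method for the relative risk nor a rule for empty cells.

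The same section gives the estimate priority over the p-value: "interpretation will focus primarily on effect size estimates and their 95% confidence intervals rather than solely on statistical significance". A general sentence adds "Estimates will be presented with two-sided 95% confidence intervals", without saying of which quantities. A model for event counts is conditional: "If the number of events per patient is analyzed, between-group comparisons will be performed using Poisson regression or negative binomial regression". It would also give a ratio.

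Section 2.3.1 describes the trial as "intended to generate preliminary data (estimates of adverse event rates) for a future randomized controlled trial". Section 2.2 sets the size at 20 infants in each group.

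**The concern.** The plan asks readers to judge safety from an effect estimate and its interval, and for yes/no events the only estimate it names is a ratio. A ratio needs events in both arms. The events that would weigh most in a judgement on FMT are individual serious ones, and Section 4.3 itself describes sepsis after FMT as rare. For such events, 20 infants per arm will often leave one arm or both arms empty.

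The difficulty is greatest when a signal appears. If all events fall in the FMT arm, the relative risk is infinite. Fisher's test still works but supplies no effect size, and the limitations in Section 5.4 rightly warn against reading a non-significant result as no effect. The named measure also fits the stated purpose loosely, because estimating AE rates for a later trial calls for absolute rates.

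**Working it through.** The plan gives no power calculation or event rate for this point, so it has no figure to reproduce.

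**Inputs.** From the documents: n = 20 per arm (Section 2.2), two-sided 95% intervals (Section 2.3.3), NEC risks of 9%, 11% and 13% (Introduction), and attrition of about 15% (Section 5.3), which would leave 17 per arm. Assumed: all other event rates, and an equal true rate p in both arms unless stated.

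**Chance of an empty arm.** Let q = (1 - p)^20.
- Control empty, so RR infinite or 0/0: q
- FMT empty and control not, so RR = 0: q(1 - q)
- At least one arm empty: 1 - (1 - q)^2

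| True rate p | Control empty | RR = 0 | At least one arm empty |
|---|---|---|---|
| 1% (assumed) | 0.818 | 0.149 | 0.967 |
| 2% (assumed) | 0.668 | 0.222 | 0.890 |
| 5% (assumed) | 0.358 | 0.230 | 0.588 |
| 9% (NEC) | 0.152 | 0.129 | 0.280 |
| 11% (NEC) | 0.097 | 0.088 | 0.185 |
| 13% (NEC) | 0.062 | 0.058 | 0.120 |
| 20% (assumed) | 0.012 | 0.011 | 0.023 |

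The last column equals one half when q = 1 - √0.5 = 0.293, that is p = 1 - 0.293^(1/20) = 5.96%. With 17 per arm the break-even is 6.97%, and the figure at 5% rises from 59% to 66%.

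**Given that some event occurs.** The chance that all events lie in one arm is 2q(1 - q)/(1 - q^2): 80% at 2% and 53% at 5%.

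**With a real harm.** Assume 2% in control and 10% under FMT. The chance that control is empty while FMT has events is 0.98^20 × (1 - 0.90^20) = 0.668 × 0.878 = 0.59.

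**What each measure gives for 3/20 FMT against 0/20 control.**
- Raw RR: 3/0, infinite. The ordinary log-scale interval does not exist.
- Adding 0.5 to each cell: RR = 3.5/0.5 = 7.0, with SE(log RR) = √(1/3.5 - 1/20.5 + 1/0.5 - 1/20.5) = 1.479, so 95% CI 0.39 to 127.
- Koopman score interval for the RR: about 0.85 to infinity.
- Fisher's exact test: p = 0.23. It falls below 0.05 only at 5 against 0 (p = 0.047).
- Risk difference: +15.0 points. The Wilson limits are 5.2% to 36.0% for 3/20 and 0 to 16.1% for 0/20. The Newcombe lower limit is 0.15 - √((0.15 - 0.052)^2 + 0.161^2) = -0.038, and the upper is 0.15 + (0.360 - 0.15) = 0.360.

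**For 0/20 against 0/20.** The RR is 0/0. The risk difference is 0 (Newcombe -16.1 to +16.1 points). The exact upper limit for each arm is 1 - 0.025^(1/20) = 16.8%.

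**The case against.** The strongest reply is that the interval method and the handling of empty cells usually belong in an analysis plan, which is not shown. A score interval for the relative risk still gives a bound with one empty arm, and Section 5.4 already expects wide intervals. This stands as far as it goes: the absence of an interval method is not the point here. But the protocol itself selects the relative risk and makes effect estimates the basis of interpretation, and a bound of about 0.85 to infinity is a weak basis.

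Three stronger readings are tempting, and the documents do not support them.
- A reader might infer that an empty arm is the likely result for NEC, or for the trial's safety result as a whole. At the Introduction's NEC risks the chance is 12% to 28%. The primary comparison of infants with at least one AE is largely unaffected, because Section 5.1 counts any departure from normal as an adverse event.
- A reader might infer that absolute rates with intervals are not planned. Section 2.3.3 defines the primary endpoint as incidence, and its general promise of 95% intervals for estimates can cover the rate in each arm. What is missing is an explicit statement for each event and an absolute between-group measure.
- A reader might infer that only a p-value would remain. Section 2.2 commits to describing every adverse event, with its classification and its relation to the intervention.

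It is also fair that RR = 0 is a defined estimate. The ratio is infinite or undefined only when control is empty: 67% at 2%, 36% at 5% and 10% at 11%. The risk difference is imprecise too, at ±16 points when neither arm has an event.

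**Conclusion.** The point holds for individual rare serious events and should be confined to them. Below a true rate of about 6% per arm, 20 infants per arm make an empty arm more likely than not (89% at 2%, 59% at 5%). The only named effect measure is then 0, infinite or undefined, with at best a one-sided or very wide interval. The risk difference and the rates in each arm stay finite in every such case. The percentages assume equal true rates in the two arms, and the 2% and 5% are illustrations, not figures from the protocol. Fisher's test and the primary comparison on at least one AE are not undermined. This is a stated choice of measure that suits these events poorly and is easily improved, not a flaw that invalidates the analysis.

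**What to change.** In Section 2.3.3, state that for each AE and SAE the report will give:
- the incidence in each arm with an exact (Clopper-Pearson) 95% interval;
- the risk difference with a score-type 95% interval (Newcombe or Miettinen-Nurminen);
- the relative risk with its 95% interval as a supplementary measure, where both arms have events.

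Stratifying the risk difference by gestational group need not be required, because the protocol does not fix how the 20 controls divide between the two gestational bands. The change takes about two sentences, standard software and no new data. Its cost is slightly more reporting.

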## Abstract

**Background/Objectives**: Necrotizing enterocolitis (NEC) is an inflammatory disease with an incidence of about one in 1000 live births, much higher in premature and low birth weight newborns. Intestinal dysbiosis is an important element in the pathogenesis of NEC, and for this reason, experimental models have been used to administer fecal microbiota transplants (FMTs) for prophylaxis and treatment of NEC with very satisfactory results. The primary endpoint of the study is safety, defined as the incidence of adverse events (AEs) and serious adverse events (SAEs) occurring from the time of intervention until hospital discharge, classified according to severity and assessed for relatedness to the intervention. **Methods**: This prospective, single-arm, open-label clinical study will include 20 infants born between 24 0/7 and 36 6/7 weeks of gestation. FMTs will be administered twice as a deep rectal infusion via a Foley catheter. The donors of the material from which the FMT will be prepared will be women in the third trimester of pregnancy. The safety of the therapy will be assessed by comparison with a control group, i.e., 20 patients who will meet the same inclusion criteria and will not meet any of the exclusion criteria, subject to the same hospital observation but without undergoing any medical/therapeutic intervention other than the collection of biological material. **Discussion**: The study will provide data on the safety and initial efficacy of FMT in this group of patients, which will allow for further research into the use of this method in the prevention of infections and NEC. Ethics: The study protocol was approved by the Bioethics Committee of the Medical University of Warsaw, Warsaw, Poland (KB/52/2025). All procedures will follow the principles of the Declaration of Helsinki. The results of the study will be submitted for knowledge translation in peer-reviewed journals and presented at national and international pediatric society conferences. Clinical Trial Registration: The study is registered at ClinicalTrials.gov: ID: NCT06333405.

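### If infants discharged without an AE are censored, the supplementary Kaplan–Meier curve for time to first AE overstates the in-hospital risk and will not match the crude proportion in the same section

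*Protocol article*

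**What the plan says.** The Abstract defines the primary endpoint as AEs and SAEs "occurring from the time of intervention until hospital discharge". Section 2.3.3 restates it as "incidence of adverse events (AEs) and serious adverse events (SAEs) during the observation period", without repeating where that period ends.

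The main comparison is of crude proportions: "The proportion of patients experiencing at least one AE or SAE will be compared between groups using Fisher’s exact test", with a chi-square alternative and relative risks with 95% confidence intervals. Section 2.3.3 then adds, on a conditional basis: "Time to first AE, if applicable, will be analyzed using Kaplan–Meier estimates and compared using the log-rank test".

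The article does not name discharge as a competing event, a cumulative-incidence estimator, or a time horizon that closes before discharges begin. Sections 2.2 and 2.3.1 build the study group from 10 infants born at 28 0/7 to 36 6/7 weeks and 10 born at 24 0/7 to 27 6/7 weeks. Section 5.3 describes stays of several weeks. Discharge times can therefore be expected to spread widely.

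**The concern.** Censoring is meant for infants whose outcome is unknown. When the risk period ends at discharge, an infant who leaves without an AE has a known outcome. Kaplan–Meier with that infant censored answers a different question: the risk of a first AE if nobody ever went home. It gives the departed infant the later hazard of those still in hospital. If the more mature and healthier infants leave first, the censoring is also informative.

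Section 2.3.3 would then yield two different figures for the until-discharge risk of a first AE, one from the crude proportion and a higher one from the curve. The same section says interpretation will rest mainly on estimates and their intervals, so a reader could take the higher figure at face value.

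**Working it through.** **Inputs.** From the article: 20 infants per group, two gestational bands of 10 in the study group, a window ending at discharge, and Kaplan–Meier for first AE. Neither an AE rate nor a distribution of stay is given, and "A formal sample size calculation based on power analysis was not performed", so there is no stated figure to reproduce. Hazards and stays below are assumptions.

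**Direction.** At each first AE with *n* infants at risk, 1−KM rises by S_KM/*n* and Aalen–Johansen rises by S_all/*n*. S_KM falls only at AEs; S_all falls at AEs and at AE-free discharges. The two are equal until the first AE-free discharge, after which S_KM is larger. So 1−KM is never below the cumulative incidence, and is above it once any first AE follows an AE-free discharge.

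**A 20-infant example (invented data).** First AEs occur on days 2, 4, 9, 20, 35 and 50. AE-free discharges occur on days 12, 14, 15, 16, 18, 20.5, 22, 25, 60, 65, 70, 75, 80 and 90.

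- After the first three AEs: S_KM = 17/20 = 0.850.
- Five discharges leave 12 at risk on day 20: 0.850 × 11/12 = 0.779.
- Three more leave 8 at risk on day 35: 0.779 × 7/8 = 0.682.
- Day 50, 7 at risk: 0.682 × 6/7 = 0.584.
- 1−KM at day 60 = 41.6%. Aalen–Johansen = 6 × 1/20 = 30.0%, which is the crude proportion 6/20.

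**Closed form.** With constant hazards *a* (AE) and *d* (discharge), 1−KM = 1 − exp(−*at*) and cumulative incidence = *a*/(*a*+*d*) × [1 − exp(−(*a*+*d*)*t*)]. For *a* = 0.02 and *d* = 0.03 per day at day 60: 1 − exp(−1.2) = 69.9% against 0.4 × [1 − exp(−3)] = 38.0%. Discharge is non-informative here, so the gap does not need sicker infants to stay longer.

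**Simulated arm.** 200,000 infants, half in each gestational band; lognormal stays (log-scale SD 0.35) with medians of 14 or 25 days (mature) and 80 days (extremely preterm). The first-AE hazard is constant within each band, −ln(1−*p*)/median stay, where *p* is the risk at the median stay. Day-60 results, 1−KM against Aalen–Johansen:

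| *p* mature / extremely preterm | In-hospital risk | Stays 14/80 d (excess, points) | Stays 25/80 d (excess, points) |
|---|---|---|---|
| 0.10 / 0.30 | 20.7% | 25.4% vs 16.6% (8.8) | 23.1% vs 16.6% (6.5) |
| 0.20 / 0.50 | about 36% | 43.7% vs 30.0% (13.7) | 40.9% vs 30.2% (10.7) |
| 0.30 / 0.70 | 50.3% | 62.7% vs 44.5% (18.2) | 59.0% vs 44.5% (14.5) |
| 0.60 / 0.90 | 74.2% | 86.3% vs 70.5% (15.8) | 83.9% vs 70.5% (13.4) |
| 0.90 / 0.97 | 91.9% | 95.8% vs 90.1% (5.7) | 95.3% vs 90.1% (5.2) |

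The gap grows with time. In the second row with stays 14/80 it is 3.7% vs 3.7% at day 3, 27.2% vs 21.8% at day 30, 43.7% vs 30.0% at day 60 and 66.6% vs 35.3% at day 120. The largest day-120 excess in any scenario was 35.3 points (85.3% vs 50.0%).

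**When it vanishes.** With all AE hazard placed in the first 3 days, the two estimates agreed at every time point.

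**The case against.** The strongest reply is that the article does not write out a censoring rule. AE-free discharged infants could be kept in the risk set to a common horizon, or the curve could stop at the 72 h monitoring period of section 4.3; either would remove the excess. Censoring rules often sit in an analysis plan, and none is shown. This stands in part: censoring at discharge is an inference. It is still the natural reading when observation ends at discharge, and the article names the estimator without any horizon or rule that avoids the problem.

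Second, first AEs may come early. Section 5.1 counts any deviation from the norm, including a rise in inflammatory markers, and section 4.3 concentrates assessment in the first 72 h. This also stands, and it is why no single size can be claimed.

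Third, with 20 infants the curve is imprecise anyway. In the example, the exact 95% interval around 6/20 is 11.9% to 54.3%, which contains 41.6%. That is true, but the excess is systematic and can only go upwards.

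A reader might also infer three stronger points that the article does not support:

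- *The log-rank test is invalid.* It remains a legitimate comparison of the AE hazard in hospital, provided discharge is non-informative.
- *Deaths would be wrongly censored.* The Kaplan–Meier sentence covers first AE. Section 4.1 makes death an SAE, so it counts as an event. Specific AEs are compared by Fisher's exact test.
- *An inflated rate will enter the later trial's design.* Section 2.3.1 speaks only of AE rate estimates, which the crude proportions supply.

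**Conclusion.** The point holds for the supplementary curve only. With AE-free discharge censored, 1−KM overstates the in-hospital cumulative risk of a first AE and disagrees with the crude proportion beside it. It would be wrong to conclude that the primary safety result is biased: the Fisher comparison and the relative risks do not use the curve.

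The direction is certain under that censoring rule. The size is not. It is negligible if first AEs fall within 72 h, and about 5 to 18 points at day 60 for assumed in-hospital risks of about 21% to 92% with the hazard spread over the stay. These figures rest on assumed stays and hazards and illustrate the effect; they do not predict this trial's results.

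**What to change.** Replace the sentence with wording such as: *If time to first AE is reported, it will be shown as cumulative incidence (Aalen–Johansen), with discharge without an AE as a competing event; only withdrawal or transfer will be censored. The log-rank test will be reported as a comparison of the AE hazard while in hospital.* With no other loss, the estimate at the last discharge then equals the crude proportion.

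An alternative is to keep Kaplan–Meier but stop it at a fixed early time, such as 72 h after FMT or after the matching time point. That covers only part of the endpoint window. Sections 4.3 and 4.4 also schedule inflammatory markers more often in recipients than in controls over those 72 h.

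Gray's test can be optional. It reflects length of stay as well as AE hazard, so an arm with shorter stays could look safer merely through less time at risk, and duration of hospitalization is itself a secondary outcome (section 5.2).

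The cost is one sentence. Days in hospital are already recorded in both groups (section 4.4), so no new data are needed. The downside is that the reported risk applies to the hospital stay only, and any between-group difference in length of stay must be considered when reading it.

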### 4.3. Monitoring the Transplant Recipients After the Procedure

Based on experience with FMT, the highest risk of developing sepsis, a rare but dangerous complication, occurs within the first six hours after the preparation is administered. Therefore, after the procedure, the patient will be continuously monitored.

The following will be assessed for the next 72 h after FMT administration:The number of episodes of oral feeding intolerance, diarrhea and the presence of blood, mucus or pus in the stool.The appearance of symptoms of infection or significant changes in vital signs (ECG, heart function and saturation—continuous measurement; blood pressure—4 times a day; temperature).The number of cases of NEC developed.Observation of other symptoms, such as convulsions, inconsolable crying and anxiety.The number of positive blood cultures and the percentage of antibiotic therapy use.Number of serious adverse events (SAEs), e.g., death, serious threat to health and/or life, and/or deterioration of health.

Blood inflammation parameters (leukocyte count, CRP and procalcitonin) will be collected before administration of the preparation (FMT1) and no later than 6–12 h after administration of FMT2, then every 12–24 h up to 72 h after FMT, depending on the patient’s condition.

A blood culture will be taken in the event of a significant increase in inflammatory parameters.

If any of the above-described criteria for temporary postponement of microbiota administration occur between FMT1 and FMT2 but resolve within 6 h (reassessment of the child’s condition after a minimum of 6 h) and do not recur within the next 6 h, the second dose of microbiota (FMT2) may be administered.

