### 5.4. Discussion

For many years, necrotizing enterocolitis has been associated with high and stable mortality rates, as well as severe complications. Despite significant progress in neonatal care, diagnosing and treating this condition remains a major clinical challenge. The available treatments are often ineffective and have side effects. Based on available studies, it is becoming increasingly clear that disturbances in gut microbiome composition play a very important role in the pathogenesis of NEC. The promising approach of restoring microbial balance using FMT could be beneficial in preterm infants at risk of NEC. Consistent experimental research shows reduced NEC incidence and reduced inflammation parameters following FMT. Although large-scale trials remain unavailable, early clinical studies suggest favorable safety, even among heavily immunosuppressed adult patients [31].

At the same time, meta-analyses do not provide clear evidence supporting the preventive effect of standardized probiotics against NEC. Although strains of Bifidobacterium and Lactobacillus may have beneficial effects, they appear insufficient to restore the natural microbiota, particularly in the context of multifactorial dysbiosis [12,13,14].

Despite numerous studies and meta-analyses evaluating probiotics in reducing NEC-related mortality and morbidity in preterm infants, ESPGHAN and AAP recommendations remain cautious. An optimal strain, dose, or combination for routine supplementation has not yet been clearly established [15,16,17,18].

We hope that this study will generate essential safety data to inform future randomized controlled trials assessing prophylactic efficacy and potential long-term benefits of FMT.

We acknowledge several important limitations of this study.

First, the open-label design may introduce detection bias, particularly for subjective safety endpoints such as feeding intolerance. Although objective definitions for sepsis and NEC (Bell’s criteria, CRP levels, blood cultures) are applied to mitigate this risk, complete elimination of assessment bias cannot be ensured.

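### The protocol names an early risk window after FMT and monitors it for 72 h, but every between-group AE comparison covers the whole stay, which dilutes an early excess

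*Protocol article*

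**What the plan says.** Protocol article, section 2.3.3, lists the between-group safety analyses:

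- Any AE or SAE: "The proportion of patients experiencing at least one AE or SAE will be compared between groups using Fisher’s exact test".
- By type: "The incidence of specific AEs will also be compared using Fisher’s exact test", with relative risks and 95% CIs.
- Events per patient, if analysed: Poisson or negative binomial regression.
- Timing: "Time to first AE, if applicable, will be analyzed using Kaplan–Meier estimates and compared using the log-rank test".

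The section sets these against the observation period, which the Abstract defines as intervention to hospital discharge. No shorter window is named for any comparison.

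Section 4.3 states that "the highest risk of developing sepsis, a rare but dangerous complication, occurs within the first six hours after the preparation is administered". It then sets a structured 72 h assessment of feeding intolerance, diarrhea, blood in the stool, infection signs, NEC, positive cultures and SAEs. Section 5.4 gives the hoped-for effect: "Consistent experimental research shows reduced NEC incidence and reduced inflammation parameters following FMT". Section 5.1 counts symptoms of infection and rises in inflammation indicators as AEs, so early risk and later benefit enter the same endpoint.

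**The concern.** The protocol places the main procedural risk in the hours after dosing, but compares the groups over a stay that section 5.3 says typically lasts several weeks. Preterm infants have AEs throughout such a stay for reasons unrelated to FMT. A whole-stay proportion lets these later events in both arms swamp an early difference. A log-rank test on first AE uses the timing, but weights all event times equally. Early excess events are therefore only part of the sum, and a lower later hazard under FMT would subtract from them.

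At stake is whether a study meant to pick up safety signals contains one formal estimate aimed at the period it monitors most closely. The emphasis on estimates over p-values does not supply one. The log-rank test yields no estimate, and the planned relative risks are whole-stay figures that are diluted in the same way.

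**Working it through.** **Inputs from the protocol.** 20 per group ("continuous recruitment of up to 40 patients in total (20 in the study group, 20 in the control group"), a two-sided test at 0.05 (section 2.3.3) and a 72 h window (section 4.3). There is no planned power to reproduce: "A formal sample size calculation based on power analysis was not performed". No AE rate, hazard ratio or length of stay is given.

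**Assumptions (not in the protocol).** Piecewise-constant hazard over 0–3 days and 3–60 days; later control risk 50% among those without an early AE; later hazard ratio (HR, FMT vs control) of 0.5, 0.7 or 1; no dropout.

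**Step 1: whole-stay risk.** Risk = 1 − (1 − early risk) × (1 − later risk), where the later FMT risk is 1 − 0.5^HR. Control with 5% early: 1 − 0.95 × 0.50 = 52.5%.

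- FMT 40% early, HR 1: 1 − 0.60 × 0.500 = 70.0%; relative risk 70.0/52.5 = 1.33.
- FMT 40% early, HR 0.7: 1 − 0.60 × 0.616 = 63.1%; relative risk 1.20.
- FMT 40% early, HR 0.5: 1 − 0.60 × 0.707 = 57.6%; relative risk 1.10.
- FMT 30% early, HR 0.5: 1 − 0.70 × 0.707 = 50.5%; relative risk 0.96.

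The 72 h relative risks are 40/5 = 8 and 30/5 = 6. The whole-stay estimate shrinks an eightfold early excess to between 1.10 and 1.33, and in the last case reverses a sixfold one.

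**Step 2: chance of p < 0.05**, simulated with 4,000 trials per row. Repeat runs differ by a few percentage points at most.

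| Early AE, FMT vs control | Later HR | Log-rank | Fisher, 72 h | Fisher, whole stay |
|---|---|---|---|---|
| 40% vs 5% | 0.5 | about 14–15% | about 72% | about 3% |
| 40% vs 5% | 0.7 | about 22% | about 72% | about 5% |
| 40% vs 5% | 1 | about 38% | about 72% | about 12% |
| 30% vs 5% | 0.5 | about 6–7% | about 46% | about 2% |
| 30% vs 5% | 1 | about 21% | about 44% | about 7% |

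The HR 1 rows show dilution by background AEs alone. A later benefit makes it worse.

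**Step 3: a different model.** With 40 days of follow-up, control risk 60% and 30% extra FMT risk within 6 h, HR 1 / 0.7 / 0.5 give log-rank 26% / 12% / 6%, Fisher at 72 h 51% / 45% / 40%, and whole-stay Fisher 6% / 3% / 3%. The pattern is the same.

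**Step 4: where the gain disappears.**

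- Small excess, 15% vs 5%, HR 1: about 6–8% for both log-rank and 72 h Fisher.
- High control rate, 50% vs 30%, HR 1: about 16–18% for log-rank and 14–17% for 72 h Fisher.
- Rare event: with 20 per group and none in controls, Fisher's p is 2 × C(20,k)/C(40,k). For k = 4 this is 2 × 4845/91390 = 0.106; for k = 5 it is 2 × 15504/658008 = 0.047. Five cases to none are needed. At a true risk of 5%, the chance of even one case in 20 infants is 1 − 0.95^20 = 64%; at 1% it is 1 − 0.99^20 = 18%.

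**The case against.** A reader might infer that the protocol itself expects harm first and benefit later, so that the hazards must cross and cancel. The text does not go that far. Section 4.3 calls sepsis rare and gives no rate, section 2.1 hypothesizes an AE profile comparable to standard care, and the benefit in section 5.4 comes from experimental research with no effect size for this trial. Crossing hazards are possible, not stated. The point does not need them, because dilution also occurs at HR 1.

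A reader might also infer that an early safety signal is likely to be missed. That does not follow either. The log-rank test is secondary and applies only if applicable. Kaplan–Meier curves would show early separation, and section 2.2 requires every AE to be described, classified and related to the intervention. The Discussion warns against reading non-significance as absence of effect. What is weak is the formal comparison, not the whole safety review.

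The case that sample size is the real limit is right for sepsis, where no choice of test helps. It is less complete for feeding intolerance and diarrhea, which are on the 72 h list and are not called rare. There the choice of window can matter at the same sample size.

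Finally, window-specific analyses are often left to an SAP, which is not shown. That lowers the weight of the point. The mismatch remains between the comparisons that section 2.3.3 does fix and the window that section 4.3 sets.

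**Conclusion.** The point holds as a poor match between analysis and stated risk, and as a cheap improvement rather than an error that hides harm. No comparison in section 2.3.3 isolates the 72 h that the protocol singles out. If early AEs are common after FMT and uncommon in controls (30–40% vs 5%), a 72 h comparison raises the chance of a significant result by about 23 to 58 percentage points over the log-rank test (44 − 21 and 72 − 14). It also gives an undiluted estimate. If the early excess is small or controls have many early AEs, there is little or no gain in power. For a rare event there is none. All power figures rest on assumed rates, no dropout (the protocol anticipates about 15% attrition) and equal ascertainment in the two arms.

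The last assumption is doubtful. After FMT, markers are taken within 6–12 h of the second dose and then every 12–24 h up to 72 h (section 4.3). In controls they are taken at least once within 72 h of day 6 (section 4.4). Because a marker rise counts as an AE, this would tend to inflate early FMT events.

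**What to change.** Add to section 2.3.3 two pre-specified comparisons of the proportion with at least one AE: (a) from dosing, or the control matching time point, to 72 h; (b) from 72 h to discharge. Report each as a risk difference with an exact 95% CI and Fisher's test, and state which of the two doses starts the clock. Keep Kaplan–Meier and log-rank as supportive; nothing needs to be removed. Report (a) a second time without AEs defined only by a rise in inflammation markers, because sampling is denser in the FMT arm.

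The cost is analysis wording. The AE and monitoring data are already planned, provided onset times are recorded finely enough to place events within 72 h. The downside is two more estimates in a small study, and a 72 h contrast that needs cautious reading because ascertainment is unequal.
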